## Abstract

Sleep difficulties, particularly symptoms of insomnia and circadian disruption, are among the primary complaints of gynecologic cancer survivors before, during, and after treatment. Moreover, difficulty sleeping has been linked to poorer health-related quality of life and elevated symptom burden in this population. Although leading behavioral sleep interventions have demonstrated efficacy among cancer survivors, up to 50% of survivors are non-adherent to these treatments, likely because these interventions require labor-intensive behavior and lifestyle changes. Therefore, there is a need for more effective and acceptable approaches to diminish sleep disturbance among cancer survivors. This manuscript describes the methodology of a two-part study guided by the Multiphase Optimization Strategy (MOST) framework to identify a streamlined behavioral sleep intervention for gynecologic cancer survivors. Three candidate intervention components previously shown to decrease sleep disturbance will be evaluated, including sleep restriction, stimulus control, and systematic bright light exposure. Participants will be adult women with a history of non-metastatic gynecologic cancer who have completed primary treatment and who report current poor sleep quality. Fifteen participants will be recruited for Part 1 of the study, which will utilize qualitative methods to identify barriers to and facilitators of intervention adherence. Results will inform changes to the delivery of the candidate intervention components to promote adherence in Part 2, where 80 participants will be recruited and randomized to one of eight conditions reflecting every possible combination of the three candidate intervention components in a full factorial design. Participants will complete assessments at baseline, post-intervention, and 3-months post-intervention. Part 2 results will identify the combination of candidate intervention components that yields the most efficacious yet efficient 6-week intervention for diminishing sleep disturbance. This is the first known study to apply the MOST framework to optimize a behavioral sleep intervention and will yield a resource-efficient treatment to diminish sleep disturbance, improve health-related quality of life, and decrease symptom burden among gynecologic cancer survivors. ClinicalTrials.gov Identifier: NCT05044975.

## Introduction

### Sleep Disturbance in Cancer Survivorship

Sleep difficulties, particularly symptoms of insomnia and circadian disruption, are common among gynecologic cancer survivors (Westin et al., 2016; Campbell et al., 2019; Palagini et al., 2021), with recent research demonstrating an estimated prevalence greater than 80% (Pozzar et al., 2021). Sleep disturbance has also been associated with poorer health-related quality of life (HRQOL) and higher symptom burden in this population (Ross et al., 2020). Difficulty sleeping is often treated with Cognitive Behavioral Therapy for Insomnia (CBT-I), the gold-standard treatment for insomnia, including among those with comorbid conditions (Schutte-Rodin et al., 2008; Qaseem et al., 2016; van Straten et al., 2017). CBT-I is a multicomponent behavioral intervention consisting of cognitive restructuring, sleep restriction, stimulus control, sleep hygiene education, and relaxation therapy (Morin and Benca, 2012). Sleep restriction and stimulus control are generally recognized as the core components driving treatment effects (Morin et al., 2006). A recent meta-analysis evaluating the efficacy of CBT-I specifically in cancer survivors found that the intervention improved multiple sleep outcomes, including sleep efficiency, sleep onset latency, wake after sleep onset, and insomnia symptom severity (Johnson et al., 2016). Another recent meta-analysis supported the efficacy of CBT-I among cancer survivors regardless of whether the intervention was delivered in-person or remotely (Ma et al., 2021). However, although CBT-I can be highly efficacious, up to 50% of cancer survivors do not adhere to the treatment as it is currently packaged, and thus do not benefit maximally from it (Matthews et al., 2012, 2013; McChargue et al., 2012; Garland et al., 2014). This may be because the intervention requires patients to make multiple, simultaneous, and often intrusive behavioral and lifestyle changes (Agnew et al., 2021). A less burdensome alternative is systematic bright light exposure, which has recently been explored as another strategy for improving sleep disturbance in cancer survivors (Wu et al., 2018, 2021; Fox et al., 2021). Results suggest systematic bright light exposure in the morning may have a beneficial impact on sleep disturbance among cancer survivors. However, effects are generally not as strong as they are for CBT-I, with research thus far limited to small pilot studies where the mechanisms underlying the effects of bright light have not been well explored.

A leading theory of sleep-wake regulation is the two-process model (Borbely et al., 2016), which posits that sleep timing and intensity depend on the interaction of a homeostatic process and a circadian process, which function independently. According to this model, the homeostatic process reflects the body’s attempts to maintain balance, in that more time spent awake leads to increased pressure to fall asleep (Deboer, 2018). The circadian process, a pacemaker managed by the suprachiasmatic nucleus of the hypothalamus, determines one’s daily rhythm for sleep and wake, leading to increased sleepiness at certain times of the day and increased alertness at others (Deboer, 2018). Thus, sleep-wake cycles and circadian rhythms separately influence sleep (Borbely et al., 2016). Sleep restriction and stimulus control, the two core components of CBT-I, both target the homeostatic process. Conversely, systematic bright light exposure targets the circadian process. Therefore, combining sleep restriction, stimulus control, and bright light may have additive or even interactive effects. One known study is currently exploring this hypothesis (Bean et al., 2020); however, it is doing so exclusively among patients undergoing chemotherapy for breast cancer. Thus, the applicability of results to cancer survivors who have completed primary treatment will be unclear. Additionally, this known study is adding systematic bright light exposure to CBT-I as a packaged intervention, thus increasing the burden associated with this already challenging treatment. To maximize benefit from the available evidence-based treatments, studies are needed that can determine what combination of behavioral sleep intervention components yields the most effective intervention while also maximizing adherence to optimize impact.

### Intervention Optimization

Multicomponent behavioral interventions are traditionally developed and evaluated as pre-bundled treatment packages and assessed *via* randomized controlled trial (RCT; Guastaferro and Collins, 2019). This is an effective and important scientific approach to identify how an intervention performs relative to a control or comparison. However, this approach is unable to identify which components of the intervention, if any, could be changed or removed to increase efficiency and decrease burden. That is to say, the effects of the individual components of the intervention, both independently and interactively, remain unknown. To address this challenge, Collins and colleagues developed the Multiphase Optimization Strategy (MOST) framework (Collins et al., 2005; Collins, 2018). MOST is grounded in engineering theory and involves three phases. Like traditional RCT-based intervention science, the MOST framework involves a Preparation phase that includes developing a conceptual model, selecting candidate intervention components based on theory and evidence, and conducting pilot testing. It also includes an Evaluation phase, in which components are bundled into a final intervention package that is then evaluated, typically *via* RCT.

What sets MOST apart is the inclusion of an Optimization phase, which occurs between the Preparation and Evaluation phases, in which candidate intervention components are evaluated using randomized experimentation to determine the impact of components individually and in various combinations. This enables identification of which components make valuable contributions to the overall program effects and what combination of components yields the greatest impact. The result is an intervention that has been optimized according to specific criteria (e.g., effectiveness, efficiency, cost) and that can achieve desired results with fewer resources and less participant burden. Of note, factorial designs are frequently used in the Optimization phase because they provide an economical framework for testing multiple components in a single study.

### The Present Study

This paper describes the procedures and methodology of a two-part study guided by the MOST framework. The first part, which is consistent with the Preparation phase of the framework, will employ a qualitative approach to identify barriers to and facilitators of adherence to sleep restriction, stimulus control, and systematic bright light exposure, three evidence-based candidate intervention components previously shown to decrease sleep disturbance among cancer survivors. The second part, which is consistent with the Optimization phase of the framework, will employ a factorial design to identify the best combination of these three components, enhanced to promote adherence per the results of Part 1, to yield a resource-efficient behavioral sleep intervention with exclusively active components. Feasibility, acceptability, and adherence will also be examined, and the potential mediating roles of sleep disturbance and circadian markers on intervention effects will be explored. This work will yield an optimized behavioral sleep intervention to diminish sleep disturbance, improve HRQOL, and reduce symptom burden among gynecologic cancer survivors.

## Materials and Methods

### Participants and Recruitment

Across both parts of the study, participants will be survivors of a non-metastatic gynecologic cancer who have completed primary treatment, are between the ages of 18 and 74, and report poor sleep quality. Part 1 of the study will include 15 participants and Part 2 will include 80, for a total sample size of 95 participants to be enrolled over 5 years. Participants will be recruited from the Robert H. Lurie Comprehensive Cancer Center of Northwestern University and the University of Arizona Cancer Center, two comprehensive cancer centers located in Chicago, IL and Tucson, AZ, United States, respectively. All potential participants will provide verbal consent to complete screening for study eligibility. Those who are eligible and subsequently enroll will provide written informed consent prior to engaging in any study activities.

### Eligibility

Potential participants will be identified through a combination of physician referral and electronic medical record screening. Study eligibility will be confirmed by participant self-report *via* a telephone screening interview. To be eligible for the study, participants must endorse or demonstrate: (1) a history of a non-metastatic ovarian, uterine, vaginal, vulvar, or cervical cancer; (2) English language proficiency; (3) age 18–74 years; (4) typical sleep onset between 9:00pm and 3:00am; (5) poor sleep quality [i.e., score > 5 on the Pittsburgh Sleep Quality Index [PSQI] (Buysse et al., 1989)]; and (6) reliable telephone and internet access.

Participants who meet any of the following criteria will be excluded: (1) diagnosis of a second primary cancer other than a non-melanoma skin cancer; (2) diagnosis of significant neurological, physiological or psychological dysfunction that could impact study participation [e.g., active psychosis, glaucoma, HIV, epilepsy, current substance abuse, active suicidality]; (3) diagnosis of sleep apnea, restless legs syndrome, periodic limb movement disorder, or narcolepsy per self-report and medical record review; (4) completion of primary anti-cancer treatment (e.g., chemotherapy, radiation therapy) <30 days prior to participation or surgical intervention <60 days prior to participation; (5) significant mental or physical decline (i.e., ≥2 mistakes on the six-item version of the Mini Mental Status Exam [MMSE] (Callahan et al., 2002) or Eastern Cooperative Oncology Group [ECOG] (Oken et al., 1982) performance status score > 1); (6) shift work; and (7) plans to travel across meridians during participation. Exclusion criteria were selected due to their known impact on study outcomes or because of potential interference with study participation.

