### Study Design

This two-part study is guided by the MOST framework. Participants in Part 1 will not be randomized, but rather will receive all three candidate intervention components simultaneously. It is well established that greater adherence predicts behavioral sleep intervention efficacy; however, knowledge of how best to increase adherence is limited (Matthews et al., 2012, 2013; Agnew et al., 2021). Therefore, upon completion of the intervention in Part 1, individual semi-structured interviews will be conducted with participants and analyzed to identify barriers to and facilitators of adherence to the three candidate intervention components. Results will inform the design and delivery of the components in Part 2 to enhance adherence. Subsequently, in Part 2, a full factorial experiment will be completed that involves eight experimental conditions (Table 1). It is important to note that this study is not an eight-arm RCT and the purpose is not to compare outcomes across each of the eight conditions directly. Rather, each main effect and interaction estimate will use data from participants in all of the experimental conditions. For example, the main effect of sleep restriction will be estimated by comparing the mean for the 40 participants in conditions 1 through 4 to the mean for the 40 participants in conditions 5 through 8 in Table 1. A detailed explanation of how factorial study designs maintain power has been previously published (Collins et al., 2009).

**TABLE 1 T1:** Experimental conditions.

Experimental condition	Sleep restriction	Stimulus control	Bright light
1	Yes	Yes	Yes
2	Yes	Yes	No
3	Yes	No	Yes
4	Yes	No	No
5	No	Yes	Yes
6	No	Yes	No
7	No	No	Yes
8	No	No	No

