#### Covariates

##### Sociodemographic and Medical Information

Sociodemographic and medical information will be gathered through participant self-report and medical chart review at screening, baseline, post-intervention, and 3-month follow-up. Sociodemographic data will include age, education, income, racial background, ethnicity, employment status, and relationship status. Medical data will include information about exclusionary and comorbid medical conditions, prescription medication use, and cancer-related information (e.g., time since diagnosis, stage at diagnosis, treatment history). Participants will also complete the Self-Administered Comorbidity Questionnaire (Sangha et al., 2003).

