#### Primary Outcomes

##### Objectively Measured Sleep

The Actiwatch Spectrum Plus (Mini Mitter/Phillips/Respironics) will be used to objectively measure sleep/wake activity at baseline, post-intervention, and 3-month follow-up. In addition to sleep/wake activity, the Actiwatch Spectrum Plus records information about amount and duration of ambient white light luminance in units of lux. Participants will wear the device, which is similar in size to a watch, on the non-dominant wrist for 7 consecutive days immediately prior to each assessment. Actiwatch Spectrum Plus data will be scored and analyzed with Actiware Sleep v6.1.2 (Phillips-Respironics, Mini Mitter, Bend, OR, United States) to calculate sleep outcomes, such as total sleep time, percent sleep, total wake time, number and duration of nighttime awakenings, sleep mid-point, and number and duration of daytime naps (defined as a minimum of 10 consecutive min of inactivity). These data will also be used to calculate circadian activity rhythms (Marler et al., 2006) and the sleep regularity index (Phillips et al., 2017), which are indicators of circadian rhythm robustness. Participants will be instructed to press the event marker on the Actiwatch when initiating sleep effort at the start of the main sleep period, when discontinuing sleep effort upon final awakening, and when taking daytime naps. When wearing the Actiwatch, participants will also complete an actigraphy log in which they will record instances of and reasons for Actiwatch removal, which will be used to inform editing of the actigraphy data (Ancoli-Israel et al., 2015).

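### The numbered eligibility criteria do not exclude women currently receiving CBT-I, another structured behavioural sleep programme or light treatment; any who enrol would dilute the contrasts for the components they already use

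*Protocol article*

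**What the plan says.** The Eligibility section gives six numbered inclusion and seven numbered exclusion criteria, used in both parts of the study. The exclusions are specific: the last two read "6) shift work; and (7) plans to travel across meridians during participation". The reason given for the list is that "Exclusion criteria were selected due to their known impact on study outcomes or because of potential interference with study participation". No criterion concerns current behavioural sleep treatment or light treatment.

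The Introduction states: "Difficulty sleeping is often treated with Cognitive Behavioral Therapy for Insomnia (CBT-I), the gold-standard treatment for insomnia". It adds: "Sleep restriction and stimulus control, the two core components of CBT-I, both target the homeostatic process". The section on candidate intervention components again presents these two as the main drivers of CBT-I efficacy. Two of the three randomised factors are therefore the core of a treatment that the article itself describes as common for poor sleepers. The third factor is morning bright light.

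Study Design explains that "the main effect of sleep restriction will be estimated by comparing the mean for the 40 participants in conditions 1 through 4" with the mean for the 40 in conditions 5 through 8. Under Part 2: Intervention Optimization, each component is coded -1 or +1 for absence or presence.

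On recorded treatment, the covariate section says: "Medical data will include information about exclusionary and comorbid medical conditions, prescription medication use, and cancer-related information". Behavioural sleep treatment and light treatment are not named there.

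**The concern.** Shift work and travel across meridians are excluded because they could disturb the outcomes or participation. Current use of one of the randomised components fits the same reason at least as well, yet it is not on the list. A woman with a PSQI score above 5 who is partway through CBT-I meets the criteria as written. She could be placed in conditions 5 to 8, where sleep restriction is absent, or in condition 8, where all three components are absent, while practising sleep restriction and stimulus control on another clinician's advice.

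If being assigned a component changes little for a woman who already uses it, she adds little to the difference between its two levels. The same applies to interactions that involve that component. Part 2 exists to decide which components to keep, so a weakened contrast raises the chance that a useful component looks inactive and is dropped.

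**Working it through.** **Inputs from the protocol article**
- Part 2 sample of 80, split 40 versus 40 for each component (Participants and Recruitment; Study Design).
- Effect size 0.40, 80% power, two-sided alpha 0.05 (Part 2: Intervention Optimization).

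**Assumed inputs, not in the documents**
- p, the share of participants already using a component whatever their assignment.
- g, the fraction of the component's effect that such women still gain when assigned to it.

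**Step 1: the plan's own power figure.** A plain two-mean comparison of 40 versus 40 with d = 0.40 in SD units gives 43% power, and 80% would need 198 participants. The planned 80% is reached if the analysis uses the baseline value and the correlation between baseline and follow-up is about 0.77, which makes the residual SD √(1 − 0.77²) ≈ 0.64. The article does not state this correlation. I use it only to start from the plan's 80%.

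**Step 2: dilution.** The expected contrast is

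0.40 × [(1 − p) + p × g].

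With g = 0 (no further gain) this is 0.40 × (1 − p). With g = 0.5 it is 0.40 × (1 − p/2).

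**Step 3: equivalent sample size.** Information on the effect scales with its square, so for g = 0 the equivalent sample is 80 × (1 − p)².

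**Step 4: power.** Power ≈ Φ(d × √80 / (2 × 0.64) − 1.96), with the residual SD unrounded.

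| Assumed p | Women of 80 | Effect, g = 0 | Equivalent N, g = 0 | Power, g = 0 | Effect, g = 0.5 | Power, g = 0.5 |
|---|---|---|---|---|---|---|
| 0% | 0 | 0.40 | 80 | 80% | 0.40 | 80% |
| 5% | 4 | 0.38 | 72 | 76% | 0.39 | 78% |
| 10% | 8 | 0.36 | 65 | 71% | 0.38 | 76% |
| 20% | 16 | 0.32 | 51 | 61% | 0.36 | 71% |

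At p = 2% with g = 0 the effect is 0.392 and power 78%.

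**Step 5: direction.** Use that exists before randomisation is spread evenly over the two levels of each component on average. It therefore shrinks the contrast and does not favour one level.

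**The case against.** The strongest reply is that including such women is a legitimate choice. Coding by assignment then estimates the effect of adding a component to whatever care women already have. The statement of rationale explains why the listed criteria were chosen and does not promise that every influence on the outcomes is excluded. This is fair: the text contains no contradiction. But the article does not present the inclusion of concurrent users as deliberate, and its stated aim is to identify which components are active.

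A second reply is that the size is unknown and the g = 0 column is a worst case. That stands. The remark that poor sleep is often treated with CBT-I gives no rate for this population, still less for treatment in progress at enrolment. The Introduction also reports that up to 50% of cancer survivors do not adhere to CBT-I, and the PSQI criterion removes women whose sleep has already recovered. Those who remain may still gain from assignment.

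Four stronger readings are tempting and are not supported:
- A reader might infer that such treatment goes unrecorded. Medical information is gathered by self-report and chart review at every assessment, and all participants keep a daily diary during the intervention. Also, "the Actiwatch Spectrum Plus records information about amount and duration of ambient white light luminance in units of lux", with the device worn "on the non-dominant wrist for 7 consecutive days immediately prior to each assessment". The full protocol may hold a suitable form item too. What remains true is narrower. The diary items show sleep timing but not whether a schedule was prescribed. Wrist readings of ambient light are not shown to detect glasses worn at the eyes. No listed item identifies the treatment itself.
- A reader might infer that the component effects are in fact pulled toward zero. That requires a non-trivial share of treated women, which the documents do not establish.
- A reader might infer that women assigned few components will seek treatment elsewhere and that the 3-month effect will then be misread as fading. This is possible, but nothing in the documents bears on it.
- A reader might take the 43% in Step 1 as proof that the planned power is wrong. It shows only that an input is unstated, which is a separate matter.

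**Conclusion.** The point holds in a limited form. The eligibility list omits a condition that fits its own stated reason and overlaps directly with the randomised components. Anyone enrolled while receiving such treatment could be counted as not having a component she is using, which would dilute its main effect and interactions. This is conditional dilution, not confounding.

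Its size rests on two assumptions that the documents do not inform: the share already treated and how much they still gain. Over an assumed 5% to 20%, the loss from 80% power is about 4 to 19 points with no further gain and about 2 to 9 points with half the gain kept. Below about 5% it is small. The case for acting is that 80 participants leave little margin and the remedy is cheap, not that harm has been shown.

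**What to change.** Add an eighth exclusion to the Eligibility section: current receipt of CBT-I or another structured behavioural sleep programme, or current use of a light-treatment device. Ask it in the existing telephone screening interview. If the full protocol already has this rule, a sentence saying so settles the point.

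Optionally, add one item at the post-intervention and 3-month assessments on whether any such treatment was started outside the study. Report the counts by component level, and repeat the component-by-time estimates as a sensitivity analysis that allows for it.

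The cost is one screening question, at most one item at two assessments that already take place, and a short amendment. The downside is that a few otherwise eligible women are not enrolled and the sample is slightly narrower.
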